### 8.2 Secondary outcomes

1. All-cause mortality at 90 days
2. Time from randomisation until death (to day 90)
3. Days alive and at home at 90 days post-randomisation
4. Ventilator-free days to day 28
5. Vasopressor-free days to day 28
6. Renal replacement therapy-free days to day 28
7. Death or disability at 6 and 12 months\*

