#### ***11.6.3 Deceased patients***

Participants enrolled in this study have septic shock and consequently the participant may deteriorate rapidly and unexpectedly. In the circumstance where a participant enrolled in the study under the process explained in 11.6.1 & 11.6.2 above, dies before consent has been obtained, we will use participants' data for the study. All attempts to contact the family and relevant circumstances prior to the death of any participant will be documented in the medical record. To seek consent from grieving family members would be stressful and inappropriate. Additionally, the study integrity and safety data would be compromised without this data.

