## **12.DATA MANAGEMENT**

### **12.1 Data collection and management methods**

Data collection will be restricted to those variables necessary to define baseline participant characteristics, the delivery of the intervention in both arms, potential confounding co-interventions, and outcomes.

All data will be collected by trained research staff at each participating site; the paper case report form (CRF) worksheet may be used to collect the data from the medical record. Each participant will be assigned a unique study number at randomisation and only non-identifying data will then be entered into a web database (electronic case record form [eCRF]) by the site research staff. Data queries will be automatically generated via the electronic data collection database.

Randomised participants will be followed up until death or 90 days post-randomisation whichever occurs first for the primary outcome and thereafter up to 12 months for secondary outcomes. Follow up will be performed by site study staff by either direct contact with the participant or their LAR (if the participant has not regained adequate capacity). In all cases where the participant regains capacity they will be responsible for the provision of their own data. References to the LAR is only relevant where the participant has not regained capacity. Full protocol data will be collected for all randomised participants. If consent for participation is withdrawn or if the participant or LAR wish to opt-out, data will not be included unless consent to do so is obtained.

Participants and/or their LAR will be asked to provide three possible points of contact (home and close family contact details) to the research staff prior to discharge. Participants (or a LAR proxy) who are alive at 6 and 12 months after randomisation will be contacted by the site research coordinator via telephone. If it is not possible to contact the participant or LAR on the telephone, a copy of the relevant questionnaires will be sent to them via post or email. If the questionnaires are completed at home a return address, stamped-addressed envelope

will be provided. The research coordinators will administer, or the participants or LAR will complete, the WHODAS functional status assessment and EQ-5D-5L quality of life assessment.

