## 6. Outcome data

- Date/s and time of initiation and cessation of invasive ventilation
- Date/s and time of initiation and cessation of vasopressor support
- Date/s and time of initiation and cessation of acute renal replacement therapy
- Vital status at ICU, hospital discharge, day 28, day 90, 6 months and 12 months post-randomisation
- ED, ICU and hospital admission and discharge dates and times, including readmissions
- ED, ICU and hospital discharge destination
- Cause-specific hospital mortality
- Rehabilitation and residential care admission and discharge dates
- Functional status at 6- and 12-months post-randomisation (as measured by the WHODAS)
- Quality of life at 6- and 12-months post-randomisation (measured using the EQ-5D-5L)

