### **13.2 Statistical and analytical plan**

The primary outcome (DAOH-D90) and other non-parametric outcomes will be analysed using quantile regression with results presented as median difference (95%CI). Mortality and other binomial outcomes will be analysed using logistic regression with results reported as odds ratios (95%CI). Time to event outcomes will be analysed using proportional hazards regression with results presented as Kaplan Meier or cumulative incidence curves where mortality is a competing risk. Functional status and quality of life will employ longitudinal analysis techniques to account for data collected at both 6 and 12 months. All analyses will account for site with participants nested within site and site treated as a random effect. Where baseline imbalance ( $p < 0.2$ ) is observed between treatment arms, sensitivity analysis will be performed adjusting for imbalanced variables. Sensitivity to missingness will be performed using multiple imputation. A secondary analysis will be conducted using a Bayesian approach to model a posterior probability of the odds ratio for days alive and out of hospital at 90

days post-randomisation between the intervention and control group with associated 95% credible interval (CrI). Statistical analysis will be performed using SAS or R and a detailed statistical analysis plan will be published or posted in the public domain prior to study completion.

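### With multiple imputation kept as a sensitivity analysis, the main analysis of death or disability would by default count every known death but drop survivors without a WHODAS, which biases the composite rate

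*Protocol*

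**What the plan says.** Section 8.2 lists as secondary outcome 7 "Death or disability at 6 and 12 months". Section 13.2 assigns mortality and other binary outcomes to logistic regression, reported as odds ratios, with site as a random effect. On missing data it has one sentence: "Sensitivity to missingness will be performed using multiple imputation". It names no other method for missing outcomes.

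The two components are ascertained differently. Section 12.2, under outcome data, lists vital status as its own item: "Vital status at ICU, hospital discharge, day 28, day 90, 6 months and 12 months post-randomisation". Section 11.6.3 adds that if a participant "dies before consent has been obtained, we will use participants' data for the study". Disability needs a completed WHODAS. Under section 12.1, participants or proxies "who are alive at 6 and 12 months after randomisation will be contacted by the site research coordinator via telephone", with post or email as the fallback.

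Section 13.2 also says: "Functional status and quality of life will employ longitudinal analysis techniques to account for data collected at both 6 and 12 months". It does not say whether this covers the binary composite. It promises a detailed statistical analysis plan.

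**The concern.** A logistic regression without imputation uses only participants whose outcome can be scored. A known death is always scored, as an event. A known survivor with no WHODAS cannot be scored and drops out. The analysed set therefore holds too many deaths relative to survivors. The usual defence of complete-case analysis, that non-response is random, does not help: even if it is random among survivors, it is not random with respect to the composite, because nobody known to be dead can be a non-responder.

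At stake are the reported event rates in both arms and, if response differs by arm, the comparison itself. Section 10.10 says that clinicians and participants cannot be blinded, so unequal response is possible. The outcome bears on the quality of survival, which section 6 gives as a reason for running this trial separately.

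**Working it through.** **Plan's own figures.** The protocol gives no event rate, missing share or power for this outcome. Its only loss figure is the 5% dropout allowance in section 13.1, set for the 90-day primary outcome. That calculation reproduces (413 per arm, 826 in total; 826 × 1.15 = 949.9; 950 / 0.95 = 1000) but does not bear on this point.

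**Inputs.**
- Mortality m = 25% at 12 months: assumed. Section 6 gives in-hospital mortality in septic shock of 22% (registry data) and 8% (the observational study).
- Disability among survivors d = 1/3: a proxy. Section 6 says one third of those treated in ICU for sepsis have not regained prior function by six months.
- WHODAS response among survivors r = 70% to 90%: assumed.

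**Formulas.** True rate = m + (1 − m)d. Complete-case rate = [m + (1 − m)rd] / [m + (1 − m)r]. Simple proportions stand in for the mixed logistic model.

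**Bias in the rate.** True rate = 0.25 + 0.75/3 = 50.0%.

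| Response | Complete-case calculation | Rate | Bias (points) |
|---|---|---|---|
| 95% | 0.4875 / 0.9625 | 50.6% | +0.6 |
| 90% | 0.475 / 0.925 | 51.4% | +1.4 |
| 80% | 0.450 / 0.850 | 52.9% | +2.9 |
| 70% | 0.425 / 0.775 | 54.8% | +4.8 |

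With m = 22% (true rate 48.0%) the bias is +0.6, +1.2, +2.7 and +4.5 points for 5%, 10%, 20% and 30% of survivors missing. With m = 8% (true rate 38.7%) it is +0.3, +0.5, +1.2 and +2.0. At 5% missing it stayed below 1 point in every scenario with mortality 8% to 30% and disability 20% to 50%.

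**Direction.** Bias = (share of participants missing) × (complete-case rate − disability rate among non-responders). At 70% response with random non-response this is 0.225 × (0.548 − 0.333) = 0.048, as in the table. The bias is upward unless non-responding survivors are disabled more often than the complete-case rate, about 51% to 55% for 90% to 70% response.

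**Difference between arms.**
- Identical arms, equal response: zero.
- Identical arms, response 75% v 85%: 0.4375/0.8125 − 0.4625/0.8875 = 53.8% − 52.1% = 1.7 points.
- Identical arms, response 70% v 90%: 54.8% − 51.4% = 3.5 points from unrounded rates. This is about one standard error: √(2 × 0.25/400) = 0.035 with about 400 analysed per arm.
- With m = 22% and 500 randomised per arm, 20% v 10% missing gives a false 1.5 points and a type I error of about 7%; 30% v 10% gives 3.2 points and about 16%.
- Mortality 21% v 25%, response 80% in both arms: the true difference 47.3% − 50.0% = −2.7 points becomes 50.0% − 52.9% = −3.0. The odds ratio moves from about 0.90 to 0.89.
- Equal true composites of 48%, mortality 22% v 17%, 20% missing in both arms: a false 0.6 points.

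**After the change.** In 4000 simulated trials with m = 22%, d = 1/3 and 20% v 10% missing at random among survivors, complete-case rates averaged 50.7% v 49.2%. Filling in disability among survivors within each arm gave 48.0% v 48.0%, the true values.

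**The case against.** The strongest reply is that this is detail for the statistical analysis plan. The sentence on imputation is one line for the whole trial. It does not mention this outcome, and nowhere is a complete-case analysis prescribed. A plan could count deaths as events and impute WHODAS among survivors. That stands in part: complete-case handling is an inference, not the protocol's wording. But section 13.2 does fix imputation as a sensitivity analysis, and a plan that follows it would carry that role forward. The longitudinal sentence is not clearly about the composite, and such a model would still lose survivors with no WHODAS at either time.

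Several stronger readings are tempting, and the documents do not support them.
- That only survivors can be missing. Vital status may be unknown, and after withdrawal or opt-out "data will not be included unless consent to do so is obtained"; some of these people may have died. With m = 22% and 20% of survivors missing, the inflation vanishes (48.0%) if 20% of deaths are missing too.
- That the rate must be inflated. The sign depends on disability among non-responders.
- That a false treatment effect will follow. This needs unequal response or a different mix of death and disability, and the protocol gives no figure for either.
- That this is the only outcome on quality of survival. Section 6 presents the primary outcome as capturing death and morbidity, days alive and at home is another secondary outcome, and quality of life is a tertiary one.

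Response of 70% to 90% is assumed, and three contact points, proxy response and the post or email fallback should help. The 5% in section 13.1, however, is not a 12-month questionnaire response rate.

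**Conclusion.** The point holds in limited form. As section 13.2 stands, the default main analysis of death or disability keeps known deaths and drops known survivors without a WHODAS, so the composite rate is biased even under random non-response among survivors. Under the stated assumptions the overstatement is about 1.4 to 4.8 points at 90% to 70% response, and under 1 point at about 5% missing. With equal response the treatment effect is barely disturbed, by about 0.3 points in the case worked. With unequal response the false difference is about 1.7 to 3.5 points for gaps of 10 to 20 percentage points. A reader might infer that the trial is set to report a spurious effect on this outcome; the documents do not show that. It is one secondary outcome, and the change is worth making because a less biased main analysis is available from methods already planned.

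**What to change.** In section 13.2, state that for death or disability at 6 and 12 months the main analysis includes all randomised participants whose data may be used and whose vital status is known. Deaths count as events. Missing WHODAS disability among survivors is multiply imputed, from a model with arm, site, baseline variables and the WHODAS at the other time point. The complete-case result and a tipping-point check, varying disability among non-responders separately by arm, become the sensitivity analyses.

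The cost is a sentence or two. Imputation is already planned, so the two analyses largely swap roles, and no extra data are needed. The downside is that the main result then relies on data being missing at random among survivors; the tipping-point check tests that reliance.

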### **13.3 Subgroup analyses**

The following subgroups will be analysed for the primary outcome:

1. Age <65 years vs ≥65 years
2. Sex
3. Lactate <3 mmol/L vs ≥3 mmol /L at baseline
4. APACHE II score <15 vs ≥15
5. Source of infection (respiratory, urinary, other)
6. Fluid volume prior to randomisation dichotomised at the median volume.

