### 9.3 Inclusion criteria

Patients will be eligible if ALL of the following criteria are met while in the ED:

1. Clinically suspected infection
2. Systolic blood pressure (SBP) <90 mm Hg or mean arterial pressure (MAP) <65 mm Hg, despite a  $\geq 1000$ ml cumulative total bolus of IV fluid administered over a maximum of 60 minutes; including pre-hospital boluses
3. Arterial or venous blood lactate >2.0 mmol/L
4. At least one dose of an IV antimicrobial has been commenced

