### **13.1 Sample size calculation**

Based on the data from the ARISE trial [10], the mean (standard deviation) of DAOH-D90 was 60(31). Assuming a clinically important increase of 7 days in the vasopressors arm, a sample size of 950 will have 90% power to detect this difference with a type I error rate of 0.05 (including a 15% inflation factor to account for the non-parametric distribution). Allowing for a 5% drop out rate, we will recruit 1000 participants to the trial. A 7 day difference in DAOH-D90 is considered clinically important and is supported by consumers.

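### Section 13.3 analyses age, lactate, APACHE II and pre-randomisation fluid volume only as two-group subgroups; if the treatment effect changes smoothly with them, a continuous interaction term would use the data better.

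*Protocol*

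**What the plan says.** Section 13.3 opens with "The following subgroups will be analysed for the primary outcome" and names six subgroups. Four are built from variables recorded on a full scale, and each is split in two:

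- "Age <65 years vs ≥65 years"
- "Lactate <3 mmol/L vs ≥3 mmol /L at baseline"
- "APACHE II score <15 vs ≥15"
- "Fluid volume prior to randomisation dichotomised at the median volume"

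Section 12.2 collects age, APACHE II and the volume of fluid given before randomisation as baseline data. A lactate value is needed for entry, since section 9.3 requires "Arterial or venous blood lactate >2.0 mmol/L". The uncut values will therefore exist.

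Section 13.3 gives no reason for any cut and mentions no analysis of these variables on their full scale. Section 13.2 plans quantile regression for the primary outcome and refers to a separate statistical analysis plan, which was not available for this review.

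**The concern.** A two-group split treats everyone on one side of the cut as alike and makes near neighbours across it different. An age of 64 is separated from 65, while a lactate of 3.1 is pooled with one of 12. Lactate is the clearest case: the entry criterion confines the low group to a 1 mmol/L band and every more severe value falls in the other group.

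Whether the effect varies with age, severity or fluid already given is what these subgroups are for. If the effect changes gradually, the split discards information and lowers the chance of seeing the change. The trial is sized for its main effect, so interaction power is limited to begin with. A null subgroup result could then be taken as evidence of a consistent effect when the test had little chance of showing otherwise.

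**Working it through.** **Inputs.** Section 13.1 states that "the mean (standard deviation) of DAOH-D90 was 60(31" days, then plans on "Assuming a clinically important increase of 7 days in the vasopressors arm", 90% power, type I error 0.05 (taken as two-sided), 15% inflation for non-normality, 950 patients, and 1000 after 5% drop-out. Section 10.1 gives 1:1 allocation. The distributions of the covariates and the shape of any effect modification are not in the protocol; they are assumptions below.

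**Reproducing the plan's figure.** Per arm, n = 2 × (31/7)² × (1.960 + 1.282)² = 412.1, so 413, or 826 in total. 826 × 1.15 = 949.9, and 950/0.95 = 1000. Both stated figures reproduce. It follows that 950 patients correspond to about 826 on the mean scale once the protocol's own inflation is taken out, so both numbers are used below.

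**Information kept by a cut.** For a linear treatment-by-covariate interaction, the efficiency of a two-group cut relative to the continuous term is the squared correlation between the variable and its cut. For a normal variable cut at c, with a share p on one side, this is φ(c)²/[p(1−p)].

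| Split (normal variable) | Kept | Lost |
|---|---|---|
| 50/50 | 64% | 36% |
| 40/60 | 62% | 38% |
| 30/70 | 58% | 42% |
| 25/75 | 54% | 46% |
| 20/80 | 49% | 51% |

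Other assumed shapes:

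- Uniform variable cut at its middle: 25% lost.
- Left-skewed age cut at 65 (18 + 77 × beta(4, 2.5), 54% at or above 65): 32% lost.
- Lactate above 2 and right-skewed, four shapes (2 + exponential with mean 1.5 or 2; lognormal with median 3.5 and sigma 0.5, or median 3 and sigma 0.6, each truncated at 2), giving 51% to 72% of patients at or above 3: 37% to 49% lost on the log scale and 53% to 69% on the raw scale.
- A true step in the effect exactly at the cut: nothing lost.

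**Interaction power, mean scale, normal variable cut at its median.** With N = 950 the standard error of the main effect is 31 × √(4/950) = 2.01, and that of the difference between two halves is 2 × 2.01 = 4.02. A difference D between the halves implies a slope of D/(2 × 0.798) per SD of the covariate, with standard error 2.01. For D = 7, z = 7/4.02 = 1.74 with the cut, against 4.39/2.01 = 2.18 with the continuous term. With N = 826 the standard errors are 4.31 and 2.16.

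| D (days) | N 950, cut | N 950, continuous | N 826, cut | N 826, continuous |
|---|---|---|---|---|
| 3.5 | 14% | 19% | 13% | 17% |
| 5 | 24% | 34% | 21% | 31% |
| 7 | 41% | 59% | 37% | 53% |
| 10 | 70% | 88% | 64% | 83% |
| 14 | 94% | 99% | 90% | 98% |

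At N = 950 the loss is about 5 points at 3.5 days, 11 at 5, 17 at 7, 19 at 8, 18 at 10 and 6 at 14. At N = 826 it is 16 points at 7 days.

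**The case against.** The strongest reply is that section 13.3 only lists subgroups. It names no interaction test and does not rule out a continuous one, and the analysis plan could add it without contradicting the protocol. Pre-specified cuts are neither an error nor a contradiction, and nothing is lost for good because the raw values are collected. This is why the point is a minor one. It does not remove it: the protocol itself fixes the two-group form, and an analysis plan that follows 13.3 will inherit that form unless it says otherwise.

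The second reply is about size, and it stands. A reader might infer from the table that cutting costs a fixed 17 or more points of interaction power. The documents do not support that. They give no interaction power, and for a median cut a loss that large arises only when the continuous test would have roughly 57% to 89% power. At N = 950 that is a difference between halves of about 7 to 10 days, which equals or exceeds the trial's whole target effect. For smaller interactions both tests are weak. Likewise, a loss of a third or more of the information is not universal: it needs a normal or right-skewed variable and a roughly linear change, and the flatter shapes above lose 25% to 32%.

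The third reply also stands in part. The figures come from a model for means, whereas section 13.2 plans median regression and section 8.1 assigns zero to every death by day 90, so the outcome has a mass at zero. In one simulation of such an outcome, under assumed shapes, the continuous term still did better but by less: 91% against 86%.

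Finally, the protocol nowhere says that a null subgroup result will be reported as consistency. That is a risk in interpretation, not a statement in the plan.

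**Conclusion.** The point holds as a conditional, minor improvement. Four variables available on a full scale are analysed only in two groups, and the low lactate group is a narrow band set by the entry criterion. Under linear effect modification and a normal covariate, a median cut keeps about 64% of the information. On the mean-scale approximation this costs about 16 to 19 points of power for differences of 7 to 10 days between halves, and clearly less for smaller or much larger ones. The direction of the gain should hold when the effect changes smoothly and roughly linearly. Its size depends on covariate distributions that the protocol does not give, and it may be smaller under the planned median regression. Where the effect truly steps at a listed cut, there is no gain.

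**What to change.** In section 13.3, and in the analysis plan, state that the treatment interaction for age, log lactate, APACHE II and pre-randomisation fluid volume will be tested with the variable kept continuous in the primary-outcome model. Pre-specify a linear form, use a restricted cubic spline as a check on it, and show the estimated effect across the range of each variable. Keep the listed cuts for display in the forest plot.

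This needs no new data, no extra patients and no change to the sample size. The small cost is that a functional form has to be chosen and written down in advance for each interaction.

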### **13.4 Interim analysis**

Following the recruitment of the first 150 participants, a review will be undertaken of recruitment rates, protocol compliance and separation between the study treatment arms.

The DSMC will review a formal interim analysis performed at 50% participant enrolment.

## **14. SAFETY**

### **14.1 Data Safety Monitoring Committee**

An independent data safety monitoring committee (DSMC), comprising experts in clinical trials, biostatistics, emergency medicine and intensive care has been established before participant enrolment and will review all trial protocols. The committee will be charged with monitoring trial safety and efficacy and overseeing the interim analysis. The DSMC may, in its absolute discretion, request assessment of any other trial data at any time.

The project manager will forward a copy of all serious adverse event (SAE) reports as soon as they become available to the DSMC or at the discretion of the DSMC, their delegated independent safety monitor. The DSMC or their delegated independent safety monitor will review all SAE reports that are received and the DSMC may report back to the management committee of the study if any further action is required.

